## Rescue Medication

- In the event of any emerging complication or deterioration, all possible measures should be taken to safeguard the health and life of a patient, notwithstanding the possibility of dropout from the study.
- The rescue medication would be AmBisome in case the patient develops worsening of symptoms of Kala-azar, and investigator decides to use an alternative antileishmanial drug, and the patient will be discontinued from study.
- A Phase 2 study was conducted to assess the safety and effectiveness of AmBisome as the first line treatment in 250 patients with primary Visceral Leishmaniasis. Except for a few AEs including lip swelling, urticaria, abdominal and back pain etc AmBisome was found to be safe and effective in a total dose of 20 mg/kg in the treatment of these patients. (*Gupta J et al, 2008*). Hence the dose of AmBisome to be used as a rescue medication in this study will be as follows:
- The rescue medication AmBisome may be given in the dose of 5 mg/kg IV on Days 1, 3, 5 and 7.

# 17. ASSESSMENT OF EFFICACY

**Efficacy:** Patients will be assessed for initial cure on the basis of splenic aspirate score at Day 30 after first dose of the study drug as follows:

| **Splenic aspirate score** | **Interpretation and action to be taken** |
| --- | --- |
| 0 | At Day 30:  Initial cure achieved; Follow-up till 6 months after study drug administration |
| +1 | At Day 30:  Repeat confirmatory splenic aspirate will be done at 15^th^ day after Day 30 aspirate (i.e. Day 45 of study)  At Day 45:  0 ‑ Initial cure achieved, follow-up till 6 months after study drug administration  1+ and above - The patient will be considered as treatment failure and will be withdrawn from study and given rescue medication as deemed fit by the PI. No further follow-up will be performed. |
| above +1 | At Day 30:  These patients will be considered as treatment failures and will be discontinued from the study and given rescue medication as deemed fit by the PI. |

## Efficacy endpoints

- Proportion of patients with Amphomul^®^ 15 mg/kg as a single dose infusion on Day 1 achieving
  - Initial cure (splenic aspirate score 0 on Day 30 or on Day 45)
  - Clinical improvement on Day 30 after study drug administration
  - Absence of fever; and >1 out of following:
    - Increase in hemoglobin concentration by >10% compared to baseline
    - Any weight gain compared to the baseline visit
    - Decrease in spleen size by >33% from baseline
  - Definitive cure:

1. Initial cure at Day 30 or Day 45
2. No clinical signs and symptoms of relapse of Kala-azar for 6 months after study drug administration. If clinical signs and symptoms of relapse of the disease is suspected at any time during the 6 month follow up, splenic aspirate shall be performed at 6 months or earlier after study drug administration.

Proportion of patients achieving all three-efficacy endpoints will be compared across the two groups.

## Efficacy evaluation

- Patient will be considered eligible for efficacy evaluation if study drug has been administered and at least one efficacy assessment has been done.
- Failure of treatment is defined as the presence of any of the following conditions:

Presence of amastigotes on splenic smear examination

Treatment discontinuation due to intolerance

- Patients who discontinued the study drug before completing the total dosage due to a DLT will be considered non-evaluable.
- Non-evaluable patients who receive any dose of study drug will be included in the safety analysis.

Clinical status will be graded on a daily basis until the patient is hospitalized and at each visit thereafter.

- - - Timing of assessments: (applying the criteria for efficacy endpoint)

First assessment will be done at Day 30 after study drug administration

Second assessment on Day 45 ‑(only for patients who have a splenic aspirate score of +1 on Day 30) if the splenic score is 0, follow-up will be performed at 6 months after study drug administration and if the splenic score is +1 and above, no further follow-up will be performed.

If the splenic score is above +1 on Day 30 or Day 45 patient will be a treatment failure and no further follow-up will be performed.

At the end of 6 months after study drug administration, only if relapse is suspected – EOS visit.

# 18. ASSESSMENT OF SAFETY

The recording of AEs is an important aspect of study documentation. It is of utmost importance that all staff members at the site involved in the study are familiar with the content of this section in order to document all AEs according to the detailed guidelines set out below.

## Definitions

### Adverse Events

An AE is any untoward medical occurrence in a patient administered a pharmaceutical product and which does not necessarily have a causal relationship with the treatment. An AE may be any unfavorable symptom, sign, syndrome or disease or even a clinically significant abnormal laboratory value, which occurs for the first time during the course of a study having been absent at baseline or, if present, worsens from baseline, regardless of the suspected cause of the event.

Additionally, they may include signs/symptoms resulting from drug overdose, drug withdrawal, drug abuse, drug misuse, drug interactions, and drug dependence.

### Adverse Drug Reactions

All noxious and unintended responses to a medicinal product related to any dose should be considered Adverse Drug Reactions (ADR). The phrase “responses to a medicinal product” means that a causal relationship between a medicinal product and the adverse event is at least a reasonable possibility, i.e., the relationship cannot be ruled out.

### Serious Adverse Events

An AE will be labeled to be SAE if it-

- Results in death
- Is life threatening
- Requires in patient hospitalization
- Prolongs existing hospitalization
- Results in persistent or significant disability/incapacity
- Is a congenital anomaly/birth defect
- Amounts to any ‘other significant clinical/laboratory event’ of major concern in the opinion of the Investigator

Examples of ‘other significant medical events’ that should be considered serious for the purposes of this study include, but are not limited to, severe early onset reaction such as anaphylaxis, vasovagal episodes, episodes of hypotonia, hyporeactivity or hyperventilation, convulsions etc.

### Unexpected/ Unlisted Adverse Event

Any AE, which is not described in the IB or whose nature, intensity or frequency, differs from what has been described in the IB or a novel event of novel nature will be considered to be an unexpected event.

### Expedited Safety Report

Any AE, which is serious, unexpected and at least possibly related to the IP qualifies for expedited reporting to EC and regulatory authorities.

## Adverse Event Collection Period and Follow up

### Start of AE collection period

Reporting of AEs for any patient will begin after administration of the study drug.

### End of AE collection period

Any AE occurring after the patient has received study drug and until the patient has stopped study participation at the last visit (6 months after study drug administration) will be reported and recorded on CRF

### Follow Up of Adverse Events

After the initial AE/SAE reports, the Investigator is required to follow-up proactively with each patient and provide further information to SIRO safety team regarding the patient’s condition.

During the study, all AEs should be followed up to the event resolution or until the patient’s condition stabilizes or the patient is lost to follow-up.

If any AE is present when a patient completes the study or if a patient is withdrawn from the study, the patient will be re-evaluated within 2 weeks. If the AE has still not resolved at this time, additional follow-up will be performed, as appropriate.

The Investigator should continue to follow-up every SAE or other AE that is considered to be related to the study drugs, until it is resolved or assessed to be chronic or stable by the Investigator. This should be documented in the patient’s medical records. This follow-up may be extended beyond the end of the study period.

## Recording of Adverse Events

### General

AEs will be assessed by the Investigator throughout the study period, during each daily visit by doing clinical examination, review of the laboratory investigations and by directly questioning the patient/patient’s LAR/impartial witness.

All AEs must be noted in the patient’s medical records and AE section of the patient's CRF daily during the study drug administration period, and till the EOS visit (6 months after study drug administration) after study completion/discontinuation/withdrawal.

If known, the diagnosis should be recorded in preference to the listing of individual signs and symptoms. As far as possible each AE should be described to include-

- duration (start and end dates)
- severity/intensity (as pert NCI-CTC criteria)
- relationship to IP (unrelated, unlikely, possibly, probably, definitely)
- influence on further administration of IP
- specific therapy
- results and consequences
- seriousness

AEs already documented in the CRF, e.g. at a previous assessment and designated as ‘ongoing’ should be reviewed at subsequent visits, as necessary. If these have resolved, the documentation in the CRF should be completed.

### Assessment of intensity

The intensity of all unexpected AEs occurring during the course of the study will be graded as follows:

##### Table 4: Assessment of intensity

| **Grading** | **Description of Intensity Grading** |
| --- | --- |
| Mild (Grade 1) | - Barely noticeable and easily tolerable - Does not interfere with functioning, Relieves without medication |
| Moderate (Grade 2) | - Sufficiently discomforting, interrupts routine activity - Symptoms have to be treated but Patient continues in the study |
| Severe (Grade 3) | - Causes severe discomfort interferes considerably with daily activities - Symptoms definitely need medical treatment, patient may not be able to continue in the study |
| Life-threatening (Grade 4) | - May lead to death, if not treated vigorously |
| Death (Grade 5) | - Death due to the AE *per se* |

### Assessment of Causality

Every effort should be made by the PI to explain each AE and assess its causal relationship, if any, to administration of the study drug.

All expected reactions would be considered related to study drug administration.

Causality of all other AEs should be assessed by the PI depending upon various factors like the temporal relationship of the AE to study drug administration, whether AE follows a known pattern of response to IP, any other cause to which the AE can be attributed or intensity of AE changes on rechallenge or dechallenge.

**Table 5: Assessment of causality of AEs**

| **NOT RELATED** | Unrelated | An AE with an incompatible temporal sequence to study drug administration and which could be explained by the patient’s clinical state or other drugs/disease states; in other words, there is no association with the study drug | |
| --- | --- | --- | --- |
|  | Unlikely | An AE with a temporal sequence to study drug administration, which makes a causal connection improbable, and which could plausibly be explained by underlying disease or other drugs/disease states |  |
| **RELATED** | Possible | An AE with a reasonable temporal sequence to study drug administration, but which could also be explained by the patient’s clinical state or other drugs/disease states | |
|  | Probable | An AE follows a reasonable temporal sequence from the time of study drug administration and is unlikely to be attributed to the patient’s clinical state or other drugs/disease states |  |
|  | Definite | The AE follows a reasonable temporal sequence from the time of study drug administration and cannot be explained by the patient’s clinical state or other drugs/disease states |  |

However, failure to assess an exact causality for an AE which is serious and initially assessed as “unclassifiable” within a period of 14 days following initial notification of an SAE to SIRO will result in the event to be deemed as causally related to the IP by default.

### Assessment of outcome

An AE can reach one of the following outcomes:

- Complete recovery from the AE
- Recovered with sequelae
- Ongoing
- Death
- Unknown

### Handling of Unresolved AEs

- If any AE is present when a patient completes the study or if a patient is withdrawn from the study, the patient will be re-evaluated within 2 weeks. If the AE has still not resolved at this time, additional follow-up will be performed, as appropriate.
- Amongst the AEs ongoing on the last study visit as per the study protocol, all the AEs that are serious or the ones, which are related to the IP and are unstable in nature, have to be recorded in the AE form
- The investigator assesses the status of the AEs.
- The AEs recorded at the time of exit are to be followed until,
  - The AEs are considered to become stable as per the investigator’s discretion, or
  - The AEs are no longer considered to be medically significant by the investigator, or
  - The database of the study is declared to be locked.
- The sponsor reserves the right to ask further information on any AE/SAE, which may be considered of interest.

## Reporting of SAEs

- Any SAE occurring during the course of the study should be treated by established standards of care to protect the life and health of the patient.
- If such treatment constitutes a significant deviation from the protocol, the Investigator should notify SIRO immediately to determine whether the patient should be dropped out from the study.
- Any SAE, irrespective of causality, must be **immediately** notified to the safety team at SIRO Clinpharm Pvt. Ltd. **by telephone ([contact], 24 hour*‑*contact - [name]).**
- This must be followed up **within 24 hours by facsimile *(+*[name]*)*** on the study specific SAE reporting form with as much detailed information regarding the event that is available.
- Investigators should not wait to receive additional information to fully document the event, before notifying SIRO of a SAE.
- The SAE reporting form should detail all relevant aspects of the AEs in question. Where applicable, information from relevant hospital case records and autopsy reports should be obtained and provided, in a blinded fashion, to SIRO.
- All SAEs should be reported within 24 hours to SIRO and, within 7 calendar days to IRB/IEC on Investigator’s knowledge of the event. Confirmation of submission to the IRB/IEC must be forwarded to SIRO.
- The event must also be recorded on the CRF AE page.

## Expedited Safety Reporting and Periodic Safety Update Reports

Any serious AE, which is unexpected and at least possibly related to the IP calls for expedited reporting to regulatory authorities (DCGI) and the IECs*/*IRBs of the sites participating in Amphomul^®^ study subject to following timelines:

- 7 calendar days for SAEs involving death and life threatening events
- 14 calendar days for SAEs involving hospitalization or prolongation of hospitalization or persistent or significant disability/incapacity or congenital anomaly/birth defect or any other significant clinical/laboratory event of major concern in the opinion of the Investigator.

As SIRO acts on behalf of the Sponsor, the regulatory reporting time clock starts when any member of SIRO safety team becomes aware of an SAE.

All other SAEs do not warrant expedited reporting to the regulatory authorities and will be informed to the above regulatory authorities and IECs/IRBs for the study sites as a part of Periodic SAE listing at 6 monthly intervals, beginning from the time the first patient is enrolled in the study at any participating site.

All Expedited Safety Reports and Periodic SAE listings of the sites participating in the Amphomul^®^ study should be submitted within 24 hours of Investigator’s receipt of the documents and confirmation of submission to the IRB/IEC must be forwarded to SIRO.

## Protocol Specific safety issues

- All AEs during the study will be graded as per NCI-CTC-AE‑v3.
- Laboratory investigations pertaining to safety analysis (hematological, biochemical and serological and urinalysis*)* will be done from screening visit onwards after starting treatment with Amphomul^®^ as mentioned in Section 14. Study Calendar.
- The evaluating parameters of safety criteria are:
  - Physical findings such as body temperature, weight, rigors/chills, nausea, vomiting, dyspnoea, hypotension, hypertension, tachycardia and any other significant clinical finding.
  - Laboratory parameters as mentioned above.
- The safety criteria shall be evaluated with the definition of change in the laboratory parameters.
- All AEs will be carefully evaluated, recorded, and reported throughout the study.

**Safety criteria (endpoints)**

- Incidence of DLTs
- Incidence of IRTs
- Incidence of nephrotoxicity and hepatotoxicity
- Incidence and frequency of AEs and SAEs (including laboratory abnormalities)

**Nephrotoxicity**

- This would be the main criterion for the analysis of safety and would be defined as grade 3 or higher increase in serum creatinine level, which will be considered as a DLT.
- However, non-DLT rise of >2 times baseline, or, a value >2 mg/dL, whichever is more, shall also be considered for overall evaluation of nephrotoxicity due to the study drug.
- Serum creatinine shall be monitored for this purpose on Day 7 of hospitalization and during subsequent visits till the end of first month.

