- Patients will be evaluated for inclusion/exclusion criteria, demography and medical history.
- Splenic aspirate will be done only if rK39 dipstick test is positive (Prothrombin time will have to be carried out before splenic aspiration and procedure will be done only if result is ≤4 seconds above the control.)
- Hematology investigations (Hemoglobin, RBC, ESR, platelets, total and differential leukocyte count)
- Biochemistry investigations including the following:
  - - Liver function tests (Serum ALT, AST, alkaline phosphatase, total bilirubin, serum albumin, prothrombin time)
    - Renal function tests (serum creatinine, BUN*)*
    - Electrolytes (sodium, potassium, magnesium)
- HIV test, HCV and HBsAg tests.
- Fasting blood sugar test
- Parascreen antigen test for detection of malarial parasites
- X-ray chest and 12-lead electrocardiogram (ECG)
- UPT (for females of child bearing potential only)
- Urine analysis (routine, microscopy)
- Previous and concomitant medications will be recorded.

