**Visit 1 - Day 7**

- Thorough physical examination will be done and vital signs assessed.
- Safety assessment (AEs, SAEs, IRTs, check for nephrotoxicity and hepatotoxicity and laboratory values for different parameters) will be done
- Laboratory investigations done:-Hematology, Renal and Liver function tests, electrolytes as outlined in the screening section
- Vital signs will be recorded
- Monitoring, recording and reporting for AEs
- Previous and concomitant medications will be recorded.
- DLT assessment will be done for all the patients

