### Safety Analysis

Safety Endpoints:

- - Incidence of DLTs
  - Incidence of IRTs
  - Incidence of nephrotoxicity and hepatotoxicity
  - Incidence and frequency of AEs and SAEs (including laboratory abnormalities)

The safety analysis will be performed on the ITT population. Proportion of patients experiencing DLTs, IRTs, nephrotoxicity, hepatotoxicity, AEs and SAEs will be tabulated. Laboratory data will be summarized and displayed, including abnormal values judged to be clinically significant.

SAE reports will be presented individually. AE data will be listed individually, coded using Medical Dictionary for Regulatory Activities (MedDRA) enhanced version. Each AE will be counted only once for a given patient. If the same AE occurs on multiple occasions, the highest severity and relationship will be assumed. If two or more AEs are reported as a unit, the individual terms will be reported as separate experiences.

Concomitant medications will be coded by using the World Health Organization Drug Dictionary (WHODD) Reference List enhanced version.

Vital sign data, physical examination results, ECG examinations results will be summarized for ITT population

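### The main renal safety criterion is only a tabulated creatinine threshold count; add a baseline-adjusted between-arm creatinine ratio, with its confidence interval, beside it

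*Protocol*

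**What the plan says.** Section 18.6 (Nephrotoxicity) fixes the measure: "This would be the main criterion for the analysis of safety and would be defined as grade 3 or higher increase in serum creatinine level". Such an event also counts as a DLT. A second tier enters the overall renal evaluation: "non-DLT rise of >2 times baseline, or, a value >2 mg/dL, whichever is more". Both tiers turn creatinine into a yes/no event.

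Section 20.2.3 states the analysis, on the ITT population (all patients who received at least one dose): "Proportion of patients experiencing DLTs, IRTs, nephrotoxicity, hepatotoxicity, AEs and SAEs will be tabulated". No between-arm difference or interval is given for these proportions. Section 20.2.2, by contrast, attaches two-sided 95% intervals to the efficacy proportions. For laboratory values in general, 20.2.3 says: "Laboratory data will be summarized and displayed, including abnormal values judged to be clinically significant". Section 10.2.2 lists laboratory values as a secondary endpoint without naming a creatinine measure.

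The data exist for every patient. The screening biochemistry lists "Renal function tests (serum creatinine, BUN"), and at Day 7 the Study Summary has "Laboratory investigations done:-Hematology, Renal and Liver function tests, electrolytes as outlined in the screening section". Day 30 and the 6-month visit carry the same panel; Day 1 and Day 45 tests are discretionary. Section 18.6 adds: "Serum creatinine shall be monitored for this purpose on Day 7 of hospitalization and during subsequent visits till the end of first month".

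**The concern.** The secondary objective (10.1.2) is comparative: the safety of Amphomul against AmBisome. Sections 9.1 and 9.2 name nephrotoxicity as a limiting toxicity of conventional amphotericin B. Patients with creatinine above 1.5 times ULN are excluded, and section 9.6 reports no clinically recognisable renal disturbance in Phase II. Threshold events may therefore be few, particularly among 125 AmBisome patients.

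If one product raised creatinine modestly in most patients, few would cross the threshold and the tabulated proportions could look alike. The descriptive summaries might show the shift, but without adjustment for baseline and with no estimate of how large a difference the data rule out. The criterion named as the main one for safety would not answer the comparative question with stated precision.

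**Working it through.** **The plan's own figures.** The only related calculation in the protocol is the efficacy sample size. Its dropout step reproduces: 400/0.8 = 500, 300/0.8 = 375, 100/0.8 = 125. No figure is given for the creatinine criterion, so there is none to reproduce.

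**Inputs.**
- From the protocol: 375 Amphomul and 125 AmBisome patients, taking all enrolled as treated.
- Assumed, not in the documents: SD of log creatinine 0.25 to 0.40; correlation r between screening and Day 7 of 0.5 to 0.7; no drift in the AmBisome arm; Amphomul creatinine uniformly 10% higher; two-sided 5% tests.

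**Few events.** The chance of no event among 125 AmBisome patients is (1 − p)^125: 53% if p = 0.5%, 28% if p = 1%, 8% if p = 2%. Observing 0/125 still allows a rate up to 1 − 0.025^(1/125) = 2.9%.

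**Continuous comparison.** SE = SD × √(1 − r²) × √(1/375 + 1/125), where the last factor is 0.1033. Power = Φ(ln 1.10/SE − 1.96), with ln 1.10 = 0.0953.
- Most favourable (SD 0.25, r 0.7): SE = 0.25 × 0.714 × 0.1033 = 0.0184. Power = Φ(3.21) = 99.9%. The 95% CI spans a factor of exp(1.96 × 0.0184) = 1.04 either way.
- Least favourable (SD 0.40, r 0.5): SE = 0.40 × 0.866 × 0.1033 = 0.0358. Power = Φ(0.70) = 76%. The factor is 1.07.

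**Threshold comparison under the same shift.** The log ratio of Day 7 to screening has SD s = SD × √(2(1 − r)). P(doubling) is 1 − Φ(ln 2/s) on AmBisome and 1 − Φ((ln 2 − ln 1.10)/s) on Amphomul. Fisher power is by exact enumeration.

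| SD, r | s | Doubling, AmBisome | Doubling, Amphomul | Fisher power | ANCOVA power |
|---|---|---|---|---|---|
| 0.30, 0.7 | 0.232 | 0.14% | 0.50% | below 0.1% | 99% |
| 0.40, 0.5 | 0.400 | 4.2% | 6.8% | 13% | 76% |

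Over SD 0.25, 0.30 and 0.40 crossed with r 0.5 and 0.7, Fisher power never exceeds 13% and ANCOVA power never falls below 76%. If AmBisome is the arm with the 10% rise, the same enumeration gives Fisher power of at most about 20%; ANCOVA power is unchanged.

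Doubling alone is a lenient stand-in for the protocol's thresholds. The second tier takes the larger of doubling and 2 mg/dL; from an assumed baseline of 0.8 mg/dL, 2 mg/dL is a 2.5-fold rise. The grade 3 tier was not computed, because its cut-offs are not in the text at hand.

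**Sensitivity to drift and size of shift.** Now let AmBisome creatinine itself rise by 10.5% (0.10 on the log scale) and set the SD of the log change directly, without baseline adjustment.
- 10% shift, SD of change 0.30: 87% continuous against 14% for doubling. SD 0.40: 64% against 19%.
- 15% shift: 99.5% against 37%, and 92% against 42%.
- 20% shift: essentially 100% against 69%, and 99% against 69%.

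The ordering holds under a uniform shift; the gap narrows as the shift and the event rate grow.

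**The opposite pattern.** Suppose instead that creatinine triples in 6% of Amphomul patients and nothing else differs. Approximate simulated power:

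| SD, r | ANCOVA | Fisher on doubling |
|---|---|---|
| 0.25, 0.7 | 64% | 99% |
| 0.30, 0.7 | 55% | 96% |
| 0.30, 0.5 | 44% | 73% |
| 0.40, 0.5 | 33% | 41% |

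Here the threshold count is the more powerful in every case.

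**The case against.** The strongest reply has four parts.

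1. *Creatinine values are not ignored.* Laboratory values are a secondary endpoint and will be summarised. Section 18.6 ties the safety criteria to change in laboratory parameters, and the Study Summary says safety will be evaluated by comparing the two groups. This stands. A reader might infer that a renal difference would be missed; the documents do not support that, because an arm-wide shift would be visible descriptively. What is absent is a between-arm estimate with its precision.
2. *A model for a laboratory variable belongs in the SAP*, and section 20.2.4 leaves tests open. This stands in part: covariates and scale are SAP detail. But the protocol itself names the main safety criterion, defines it by thresholds and states that its proportions are tabulated. That is a stated choice of measure, not a blank.
3. *The power advantage follows from assuming a uniform shift.* This stands. A reader might infer that thresholds discard nearly all the information, or that ANCOVA should become the main renal comparison. The second simulation contradicts both as general statements, and the documents do not say which pattern of injury to expect.
4. *Thresholds capture clinically important harm, and there is no safety hypothesis.* This also stands. A 10% rise is about 0.08 mg/dL on an assumed 0.8 mg/dL and may be clinically minor. It is a reason to keep the counts, not to leave the comparative objective without a renal estimate.

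**Conclusion.** The concern holds in a limited form. The main safety criterion is threshold-only and its proportions are only tabulated, so a modest arm-wide rise in creatinine would be displayed but not estimated or compared with stated precision. Under the assumed uniform 10% rise on Amphomul with no comparator drift, power is about 76% to 99.9% for the adjusted continuous comparison, against at most about 13% for doubling. The SD, correlation, shift and drift are all assumptions, and other choices move both figures. Where injury is concentrated in a few patients the ranking can reverse. The case is therefore for using both measures, not for demoting the thresholds. It is a cheap improvement to a secondary objective and does not affect the primary efficacy conclusion.

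**What to change.** In section 20.2.3, for the ITT population and beside the threshold proportions (neither replacing them nor ranking above them), add:

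- an ANCOVA of log serum creatinine at Day 7, repeated at Day 30, on treatment, log screening creatinine and centre, reporting the ratio of geometric means (Amphomul to AmBisome) with its 95% CI;
- the between-arm difference in each nephrotoxicity threshold proportion with its 95% CI.

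The screening value is the baseline, because Day 1 tests are discretionary. Centre belongs in the model because randomisation is by centre and assays are done in local laboratories. The clinical definitions stay as they are.

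Cost: one extra model and one interval per threshold, with no new visit, sample or patient. The drawback is that a clear difference in means may be clinically minor, so the ratio must be read with the threshold counts.
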